
##### Improvement in Parameters as Part of Comprehensive Geriatric Assessment (CGA)

CGA includes following specific measurements:

Basic ADL: Participants will be evaluated for basic ADL using the Barthel index (Mahoney and Barthel, 1965), which includes 10 items to assess basic self-care abilities, such as feeding, transfer from bed to chair, bathing, bowel control, and bladder control, where the score ranges from 0 (complete dependence) to 100 (complete independence).Instrumental ADL: Participants will also be assessed for instrumental ADL using the Lawton index (Lawton and Brody, 1969), which includes 8 items, such as using the telephone, shopping, and handling medication, where the score ranges from 0 (low function) to 8 (high function).Depressive symptoms: Participants will be evaluated for depressive symptoms using the 15-item Geriatric Depression Scale (Yesavage et al., 1982), where the score ranges from 0 to 15, with higher scores indicating more depressed mood.Physical performance: For all participants, usual gait speed over a distance of 2.4 m at the mid-point of the walkway that has both acceleration and deceleration zones (1 m, respectively) will be measured twice and a mean value will be calculated (Guralnik et al., 1994). Both right- and left-hand grip strengths will be measured using a standard digital hand grip dynamometer (Takei Scientific Instruments Co., Ltd, Japan) at standing position with shoulder adducted and neutrally rotated and elbow in full extension (Watanabe et al., 2005). One-leg standing tests will also be performed on all participants (Michikawa et al., 2009) using the one-leg standing test to measure how long (in seconds) each participant in bare may be able to stand unassisted on one leg as long as possible with eyes open for up to 60 s, and an average of left and right one-leg standing times will be calculated.Physical frailty and sarcopenia: Physical frailty will be defined for all participants based on the frailty phenotype proposed by Fried et al. in the Cardiovascular Health Study (Fried et al., 2001), which consists of shrinking, weakness, slowness, self-reported exhaustion, and low physical activity. In addition, to determine the presence or absence of sarcopenia (Chen et al., 2014; Cruz-Jentoft et al., 2019), appendicular muscle mass (AMM) will be measured in all participants by bioelectrical impedance analysis, and skeletal muscle mass index will be calculated as AMM divided by height squared (kg/m2).History of falls and fall risk: All participants will also be examined for any history of falls within the past 12 months. The Fall Risk Index (Kikuchi et al., 2009) consisting of 21 questions, including the following 3 subcategories, physical function (8 items), geriatric syndrome (8 items) and environmental hazards (5 items) will be used to detect their risk of falls, where each item receives a score of 1 (risk present) or 0 (risk absent), with a higher sum of scores indicating a higher risk of falls.Nutritional status: All participants will be assessed for their nutritional status using the Mini-Nutritional Assessment Short-Form (Rubenstein et al., 2001) composed of 6 questions, where the score ranges from 0 to 14, with a higher score indicating better nutritional status.Intakes of nutrients and foods: All participants will be assessed at baseline and at 18-month follow-up with the Food Frequency Questionnaire (Sasaki et al., 2003), which is designed to assess the average intake of 47 foods and beverage to estimate their daily food-group consumption and nutrient intakes.Appetite: Participants will also be assessed for their appetite using the Simplified Nutritional Appetite Questionnaire (Nakatsu et al., 2015), where the total score ranges from 4 to 20, with a higher score indicating a better appetite.Social network: The Lubben Social Network Scale 6 (Lubben et al., 2006) composed of 6 questions will be used to assess each participant's social network, where the score ranges from 0 to 30, with a higher score indicating better social network.Social participation: Participants will also be assessed for their social participation by a questioner about their social participation in eight types of groups (Kanamori et al., 2014): (1) neighborhood associations/senior citizen clubs/ fire-fighting teams (Local Community); (2) hobby groups (Hobby); (3) sports groups or clubs (Sports); (4) political organizations or groups (Politics); (5) industrial or trade associations (Industry); (6) religious organizations or groups (Religion); (7) volunteer groups (Volunteer); and (8) Others.

##### Improvement in Blood and Urinary Markers

Blood and urinary markers assessed in all participants at baseline and follow-up will include total protein, albumin, aspartate aminotransferase, alanine aminotransferase, γ-glutamyl transpeptidase, total cholesterol, high density lipoprotein-cholesterol, triglyceride, creatinine, eGFR, blood urea nitrogen, sodium, potassium, chloride, calcium, phosphorus, free triiodothyronine, free thyroxine, thyroid stimulating hormone, rapid plasma reagin, treponema pallidum hemagglutination, brain natriuretic peptide, vitamin B1, vitamin B12, folate, urine glucose, urine protein, occult blood in urine, and u-Alb/Cr. In addition, all participants will be assessed at baseline for their apolipoprotein E phenotype.

#### Adverse Events and Serious Adverse Events

To evaluate the safety of the intervention, all adverse events and serious adverse events will be monitored during this trial. Information to be collected about adverse events will include their date of onset, severity, associated treatment, consequences, and causation. Serious adverse events will be reported to the principal investigator, IRB, and co-researchers immediately.

### Interventions Procedures

#### Intervention Arm

The intervention group will participate in multi-domain intervention programs intended to promote: (1) management of metabolic and vascular risk factors; (2) physical exercise and self-monitoring of physical activity; (3) nutritional guidance; and (4) social participation.

##### Management of Metabolic and Vascular Risk Factors

While participants will be treated for T2DM, hypertension, and dyslipidemia in accordance with clinical guideline recommendations in Japan, they will be treated for T2DM based on the Treatment Guidelines for Elderly Patients with Diabetes Mellitus 2017 issued by the JDS/JGS Joint Committee (Japan Diabetes Society (JDS)/Japan Geriatrics Society (JGS) Joint Committee on Improving Care for Elderly Patients with Diabetes, 2017), which recommend that the glycemic target (HbA1c) be determined for each patient by taking into account his or her background characteristics and health status and classifying the patient into 1 of the following 3 categories: category I (intact cognitive function and ADL), category II (mild cognitive impairment to mild dementia or impairment of instrumental ADL), and category III (moderate or severe dementia, impairment of basic ADL, or presence of multiple comorbidities). As a specific feature of these categories, the lower limit of each glycemic target is specified for those receiving drugs associated with high risk of severe hypoglycemia, for example, insulin, sulfonylureas, and glinides. In this trial focused on subjects classified as category II, therefore, the upper limit of the glycemic target is to be set at 7.0% for patients not receiving these drugs, while the upper and lower limits of the glycemic target are to be set at 8.0% and 7.0%, respectively, for those receiving these drugs. Additionally, those in the intervention group will undergo CGM assessments to avoid hypoglycemia and glycemic fluctuations; while, likewise, those in the control group will undergo CGM assessments, clinicians will be blinded to the results of CGM assessments in these patients.

##### Physical Exercise and Self-Monitoring of Physical Activity

All participants will engage at least twice a month in a physical exercise program provided at participating institutions by study physiotherapists or trained instructors, which consists of aerobic exercise, muscle strength training, postural balance retraining, and dual-task training, namely “cognicise” (“cogni” for cognition + “cise” for exercise), involving physical and cognitive tasks. The combined activity program intervention including cognicise was shown to improve cognitive and physical performance in older adults with MCI (Shimada et al., 2018). This program will be composed of a 5-min medical check (blood pressure, pulse rate), a 15- to 20-min training including stretching, muscle strength exercise and postural balance training, a 5-min rest, a 20- to 30-min aerobic exercise, a 5-min rest, and a 20- to 30-min dual-task training. The aerobic exercises, including stair stepping and endurance walking will be performed with the mean aerobic exercise intensity set as moderate intensity according to the Karvonen formula: Target heart rate [HR] = [40–60% × (maximum HR – resting HR)] + resting HR. The maximum HR will be estimated for each participant by using the age-predicted maximal HR formula (220 – age). All participants will be assessed for HR immediately after an aerobic exercise based on their pulse rates. The participants will also be recommended to conduct daily home-based muscle-strengthening exercises, walking, and dual-task training at least twice a week, as well as to self-monitor these activities using study-provided booklets and pedometers.

##### Nutritional Guidance

Based on the JDS/JGS Joint Committee guidelines (Japan Diabetes Society (JDS)/Japan Geriatrics Society (JGS) Joint Committee on Improving Care for Elderly Patients with Diabetes, 2017), nutritional counseling sessions will be conducted individually by registered dieticians at each medical examination (performed approximately once every two months). Nutritional counseling for the participants include guidance on (1) appropriate energy intake (total energy, carbohydrate, protein, lipid, fiber, salt) to improve their glycemic control and cognitive and physical condition including frailty and sarcopenia; (2) improvement of lifestyle and dietary behavior through smoking cessation and reduced alcohol consumption; (3) intake of dietary staples (cooked rice, bread, or noodles), main dishes (fish, chicken, soybeans and soybean products), and side dishes (vegetables and seaweeds) based on the place mat to increase dietary diversity; and (4) chewing and swallowing function and oral care.

Additionally, participants will be requested to monitor their body weight, start of meal times, and dietary diversity every day using a study-provided place mat illustrating dietary variety (Figure 3) and a dietary diary. Participants will be instructed to take well balanced diet and increase dietary diversity arranging dietary staples, main dishes, side dishes, soup, fruits, and milk and dairy products on a study-provided place mat. Moreover, dietary diary will be reviewed by dieticians in nutritional counseling session, and their feedback will be given to the participants. Dieticians will also provide two kinds of foods, which include: rice with mixed grains to increase fiber intake; canned mackerel, salmon, and sardine to increase intake of proteins, eicosapentaenoic acid (EPA), and docosahexaenoic acid (DHA); fish sausage to increase intake of proteins and calcium, and cooking recipes at every counseling session.

**Figure 3 F3:**
[figure not shown]
Place mat illustrating dietary variety. Subjects are instructed to take well-balanced diet and increase dietary diversity arranging dietary staples (Cooked rice, bread, or noodles), main dishes (fish, meat, soybeans and soybean products), side dishes (green and yellow vegetables and seaweeds), soup, fruits, and milk and dairy products on a place mat.

##### Social Participation

To promote social participation, participants will be requested to go out at least three times a week. Moreover, participants will be requested to monitor their social activities including taking care their grand-children, doing work/volunteer work, face-to-face conversation, shopping/eating-out, and participating in organizations or groups by using a study-provided booklet every day. Again, to encourage an active lifestyle, a meeting will be heled after each physical exercise session, where participants discuss their physical, social, and cognitive activities among themselves.

#### Control Group

Participants in the control group will receive usual care and treatment for T2DM based on the Treatment Guidelines for Elderly Patients with Diabetes Mellitus 2017 as in the intervention group. Additionally, at baseline, they will receive general instructions on prevention of dementia including the benefits of physical activities, healthy diet, cognitive activities, and social participation.

### Statistical Considerations

#### Sample Size

Using the open source sample size calculator (http://www.openepi.com/SampleSize/SSMean.htm), the sample size was calculated based on preliminary data from MMSE assessments over 1-year (1.03 ± 0.36 years) in 83 patients with MCI and T2DM classified into category II among the Memory Clinic at the NCGG, since no multi-domain intervention trials have been conducted to date in this population. The mean change in MMSE score among 83 patients was −1.45 ± 3.55. Of these, the optimally controlled group (n = 30) showed a mean change in MMSE score of −0.33 ± 2.58. Based on these preliminary data, it was hypothesized that the present study is likely to detect differences in change of cognitive function between the intervention and control groups (intervention group vs. control group, −0.33 ± 2.58 vs. −1.45 ± 3.55). With a two-sided significance level of 5% and a statistical power of 80%, the total sample size required for the unpaired *t*-test was calculated as 242. In addition, dropout rates at final follow-up is estimated to be 15–20% at each institution, thus a total of 300 patients are required.

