### Eligibility Criteria (Inclusion/Exclusion Criteria)

Table 1 shows the inclusion and exclusion criteria for the J-MIND-Diabetes trial. In order to focus on those at increased risk of dementia, this trial focuses on T2DM patients who are classified into category II (mild cognitive impairment to mild dementia) based on the “Glycemic Targets for Elderly Patients with Diabetes” as they were put forth by the JDS/JGS Joint Committee (Japan Diabetes Society (JDS)/Japan Geriatrics Society (JGS) Joint Committee on Improving Care for Elderly Patients with Diabetes, 2017). Therefore, patients are found eligible for the J-MIND-Diabetes trial if they (1) are diagnosed with T2DM, (2) are aged 70-85 years at enrollment, (3) have no or mild impairment of basic activities of daily living (ADL) [Barthel index (Mahoney and Barthel, 1965) score of 80 or more], (4) are mildly cognitively impaired [the Japanese version of the Montreal Cognitive Assessment (MoCA-J) (Fujiwara et al., 2010) score of less than 26], (5) have a Mini-Mental State Examination (MMSE) (Folstein et al., 1975) score of 21-30, (6) are outpatients or those who have a stable clinical course for more than 4 weeks after their last hospitalization or institutionalization and whose medical examination classification need no change during the monitoring period, (7) are accompanied by a co-participant (study partner), and (8) provide written informed consent on their own or via their study partners.

**Table 1 T1:** Inclusion and exclusion criteria for the J-MIND-Diabetes trial.

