#### Randomization and Blinding

In this open-label intervention study, participants will be centrally randomized at a 1:1 allocation ratio into intervention and control groups using the stratified permuted-block randomization methods based on the following stratification variables:

Institutions (1–15 institutions).Age at enrollment (70–77 years vs. 78–85 years).Glycemic control relative to the glycemic targets recommended by the JDS/JGS joint committee (optimally controlled vs. poorly or excessively controlled).Drugs potentially associated with severe hypoglycemia such as insulin, sulfonylureas and glinides (those receiving these drugs vs. those not receiving these drugs).

The randomization sequences will be generated by a trial statistician ([name]) by using Proc Plan in SAS version 9.4 (SAS Institute, Cary, NC, USA). Study participants and research staff including investigators and clinicians at each institution will be unaware of the randomization sequences and block size. Research staff responsible for primary outcome data collection will also be blinded to group assignment, to which, however, the intervening research staff and the participants will be not blinded.

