#### Data Analyses

Data will be presented as means, medians, standard deviations, ranges and interquartile ranges for continuous and ordinal variables, and counts and percentages for categorical variables. Differences in baseline clinical characteristics between the intervention and control groups will be examined for significance by using the *t*-test or the Mann-Whitney U test for continuous variables and by the chi-squared test or the Fisher's exact test for categorical variables, as appropriate.

To evaluate differences in cognitive changes from baseline at 18-month follow-up between the intervention and control groups, the mixed-effects model for repeated measures (MMRM) with an unstructured covariance structure will be conducted using groups, time of the visit, group by time interaction, and baseline composite cognitive score as covariates. For the secondary continuous variables, the same analyses using MMRM will be performed. For the secondary categorical variables, logistic regression analyses or chi-squared tests will be conducted as appropriate. Frequencies of adverse events and serious adverse events will be summarized and compared between the intervention and control groups by using the chi-squared test or the Fisher's exact test.

All statistical analyses will be performed using SAS 9.4 (SAS Institute, Cary, NC, USA). *P*-values <0.05 will be considered statistically significant.

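### The stated 80% power rests on giving the intervention arm the SD of the 30 optimally controlled pilot patients (2.58); with an SD of 3.00 to 3.55 in that arm, the same calculation gives about 76% to 69%

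*Protocol article*

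**What the plan says.** The Sample Size section uses about one year of MMSE data from 83 memory-clinic patients with MCI and type 2 diabetes in category II.

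- Control arm, from the whole series: "The mean change in MMSE score among 83 patients was" −1.45 ± 3.55.
- Intervention arm, from a subset of the same series: "the optimally controlled group (n = 30) showed a mean change in MMSE score of" −0.33 ± 2.58.

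These become the planning assumption: "intervention group vs. control group, −0.33 ± 2.58 vs. −1.45 ± 3.55". With a two-sided 5% level and 80% power, the unpaired t-test needs 242 patients. With 15–20% dropout the plan enrols 300.

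On who enters the trial, Eligibility Criteria says "this trial focuses on T2DM patients who are classified into category II". Optimal glycaemic control is not required. Table 1 excludes only extremely poor control (fasting plasma glucose above 250 mg/dl, or moderate or severe urinary ketones). Randomization and Blinding lists glycaemic control as a stratification factor: "optimally controlled vs. poorly or excessively controlled". The primary analysis in Data Analyses is an MMRM with "baseline composite cognitive score as covariates" alongside group, visit and their interaction.

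**The concern.** The difference in means and the SD in each arm are separate inputs. The 1.12-point difference can stand as an assumed effect of the whole package, although it comes from a non-randomised contrast between a subgroup and the series that contains it. The SD of 2.58 is harder to defend. It describes patients who were already well controlled, whereas the intervention arm will be a stratified sample of all control statuses, as will the control arm.

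Carrying 2.58 over to that arm assumes that the package does two things: it moves the mean by 1.12 points, and it makes patients' changes much more alike. The section gives no reason for the second. If the spread does not narrow that far, the power at the plan's own difference is below the stated 80%, without assuming any smaller effect.

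**Working it through.** **Inputs, all from Sample Size unless noted.** Difference −0.33 − (−1.45) = 1.12; SDs 2.58 and 3.55; two-sided 5%, 80% power, so (1.96 + 0.8416)² = 7.849; 1:1 allocation (Randomization and Blinding); 15–20% dropout from 300, which leaves 255 to 240 evaluable, or 127.5 to 120 per arm.

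**1. Reproduce the plan.** n per arm = 7.849 × (2.58² + 3.55²)/1.12² = 120.5, so 121 per arm and 242 in total. This matches. The arithmetic is right; the question is the input.

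**2. What 2.58 implies.** 2.58²/3.55² = 0.53, a 47% smaller variance of change in the intervention arm.

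**3. The rest of the pilot series.** From the plan's own figures, the other 53 patients have
- mean (83 × −1.45 − 30 × −0.33)/53 = −2.08;
- SD √[(82 × 3.55² − 29 × 2.58² − 58.9)/52] = 3.88, where 58.9 is the between-group sum of squares.

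So 2.58 belongs to the less variable part of the series.

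**4. Plausible SDs for a mixed intervention arm.**
- If every patient shifts equally, the SD stays at 3.55.
- If the other 53 move to the optimal mean of −0.33 and keep their own spread, the SD is √[(29 × 2.58² + 52 × 3.88²)/82] = 3.45.
- If the spread narrows somewhat, 3.00 is an illustrative lower value. This is an assumption; the document gives no figure.

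**5. Power at 1.12 points, control SD 3.55, 121 per arm.** Power = Φ(1.12/√[(s² + 3.55²)/121] − 1.96), where s is the intervention-arm SD:
- s = 2.58: Φ(2.807 − 1.96) = 80%
- s = 3.00: Φ(2.651 − 1.96) = 76%
- s = 3.45: Φ(2.489 − 1.96) = 70%
- s = 3.55: Φ(2.454 − 1.96) = 69% (noncentral t: 68.6%)

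**6. With 300 enrolled.**
- s = 3.55: 71% at 15% dropout, 69% at 20%.
- s = 3.00: 78% and 75%.

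**7. Difference detectable with 80% power at SD 3.55 in both arms.** 2.8016 × 3.55 × √(2/127.5) = 1.25 points at 15% dropout; 2.8016 × 3.55 × √(2/120) = 1.28 points at 20%.

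**8. What baseline adjustment would have to supply.** At SD 3.55 in both arms, the t-test needs 7.849 × 2 × 3.55²/1.12² = 157.7 per arm. To recover 80% with 121, adjustment must cut the residual variance to 121/157.7 of its size, which takes a baseline–change correlation of √(1 − 121/157.7) = 0.48. The document gives no correlation.

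**The case against.** The best defence is that the plan states one coherent hypothesis: treated patients will change as the optimally controlled group did, so that group's mean and SD belong together. Glycaemic targets and CGM to avoid hypoglycaemia and fluctuation are part of the intervention, and preventing large declines could well narrow the spread. This stands to the extent that the SD under treatment is unknown and 3.55 is also an assumption. It does not rescue 2.58. The section does not make the argument, and both arms are treated under the same 2017 guideline. The 2.58 is also imprecise: from 30 patients, assuming normality, its 95% interval is about 2.05 to 3.47.

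Three further points stand and limit the claim.

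- The trial does not take patients of any glycaemic status. It excludes extremely poor control and several comorbidities, and no such exclusions are stated for the pilot series. So 3.55 is itself borrowed; assuming normality, its 95% interval is about 3.08 to 4.19. It is the more cautious planning value, not a known one.
- The 69% is the unfavourable end of a range, which is why the range is shown.
- All these figures are for an unpaired t-test on one-year MMSE change. The primary analysis is a baseline-adjusted MMRM on an 18-month composite, and it can also use the 6-month data of later dropouts. As an illustration, with 300 enrolled, 15% dropout, a baseline–change correlation of 0.3 and an intervention-arm SD of 3.0 to 3.2, power would be 79–81%; at 3.55 it would be 75%.

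**Conclusion.** The concern holds as a fault in a planning input. On the scale that the plan itself uses to justify 300 patients, 80% power at 1.12 points needs an unargued 47% cut in the variance of change. For intervention-arm SDs from 3.00 to 3.55, the planned 242 evaluable patients give about 76% down to 69%. This rests on a control SD of 3.55, the plan's own difference, and the assumption that a mixed arm is at least as variable as 3.00.

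A reader might infer two stronger things. One is that the trial itself has only 69% power and would miss a real effect about 30% of the time. The documents do not support this: the power of the planned MMRM on the composite cannot be derived from them. The other is that the trial is 74 evaluable patients short (316 against 242) and must enrol more. That shortfall holds only if the SD is 3.55; at 3.00 the requirement is 272 evaluable, a gap of 30. With the treated-arm SD unknown and the gain from adjustment unstated, the documents do not justify a larger trial. They do justify correcting the stated power.

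**What to change.** Keep 300 enrolled and revise the Sample Size section:

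- Use SD 3.55 in both arms as the planning value, or show results for an intervention-arm SD from 3.00 to 3.55. Keep 1.12 points and call it an assumed difference.
- Replace the stated 80% with about 69–71% (SD 3.55, 20–15% dropout), rising to 75–78% if the SD is 3.00.
- Give 1.25 to 1.28 points as the difference detectable with 80% power at SD 3.55.
- State that these figures are for the MMSE t-test and not for the baseline-adjusted MMRM on the composite. If the gain from baseline adjustment is relied on, state the assumed correlation; about 0.48 would be needed to recover 80% at 242 evaluable.

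This needs no extra patients and uses figures already in the section, apart from the illustrative 3.00. The cost is a less favourable stated power.
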